### Outcome measures

2.8

The primary outcome is pain intensity, measured using the Numerical Pain Rating Scale (NPRS). Secondary outcomes include functional disability assessed by the Oswestry Disability Index (ODI), health-related quality of life measured by the 36-Item Short Form Health Survey (SF-36), and neuromuscular function evaluated through surface electromyography (sEMG) parameters: %MVIC (normalized root mean square expressed as a percentage of maximum voluntary isometric contraction) and mean power frequency (MPF). Assessments will be conducted at baseline (week 0) and immediately post-intervention (week 4). The NPRS, ODI, and SF-36 will also be reassessed at weeks 8 and 12.

#### Numerical pain rating scale (NPRS)

2.8.1

The NPRS is a standardized instrument for assessing pain intensity in patients with postpartum low back pain, utilizing an 11-point numerical rating scale ranging from 0 (no pain) to 10 (worst imaginable pain). Participants select the number that best reflects their current pain level. For chronic low back pain, a 2-point change on the NPRS represents the minimal clinically important difference (MCID) (21).

#### Oswestry disability index (ODI)

2.8.2

This questionnaire assesses functional disability in patients with postpartum low back pain across ten domains: pain intensity, personal care, lifting, walking, sitting, standing, sleeping, sex life, social life, and traveling. Each domain is scored from 0 to 5, yielding a total raw score between 0 and 50. For analytical purposes, the raw score is multiplied by 2 to produce a standardized percentage score from 0 to 100, with higher scores indicating more severe disability and greater functional limitations in daily activities (22).

#### 36-item short form health survey (SF-36)

2.8.3

The SF-36 comprises 36 items that assess the impact of pain on daily health across eight dimensions and is widely used in clinical research. Scores range from 0 to 100, with lower scores reflecting poorer quality of life (23). In this study, a 30% improvement from baseline in the SF-36 score will be considered clinically meaningful (24).

#### Surface electromyography (sEMG) signal acquisition and analysis

2.8.4

Surface EMG signals will be recorded from the bilateral erector spinae, multifidus, rectus abdominis, external oblique, internal oblique, and transversus abdominis using a Delsys Trigno wireless sEMG system (2000 Hz sampling rate, 10–500 Hz bandwidth). These muscles were selected as they represent the primary lumbopelvic stabilizers, encompassing both the lumbar extensors and the abdominal wall muscles, whose coordinated activation is essential for core stability. Electrodes will be positioned in accordance with SENIAM guidelines (25). Prior to attachment, the skin will be shaved, abraded, and cleaned.

The testing protocol will comprise two parts: functional tasks and maximal voluntary isometric contraction (MVIC). Measurements will be taken before the intervention and after 4 weeks of training. Functional tasks will include prone trunk extension (erector spinae and multifidus), supine curl-up (rectus abdominis), supine rotational curl-up against resistance (external and internal obliques), and abdominal drawing-in (transversus abdominis). Each movement will be held for 3 s and repeated three times. During MVIC testing, participants will perform resisted movements specific to each muscle (e.g., prone resisted trunk extension and supine resisted curl-up) and sustain the contraction for 3 s, with three repetitions. The order of the functional tasks will be fixed across all participants to ensure consistent testing conditions. A 1-min rest interval will be provided between each functional task to minimize muscle fatigue. MVIC testing will be performed after all functional tasks are completed, with a 2-min rest period before the first MVIC trial to allow for full recovery. For %MVIC calculation, the RMS value from each of the three 3-s functional task repetitions will be averaged, and this mean will be normalized to the highest RMS value recorded during any of the three MVIC trials (i.e., peak MVIC), following standard sEMG normalization practices. For MPF, the mean power frequency will be calculated from the same analysis window (1-s epoch centered on the middle of each 3-s contraction) and averaged across the three repetitions.

Participants will be instructed to perform each task to the best of their ability without exacerbating pain. If a participant reports pain that prevents completion of a task as described, the task may be modified (e.g., reduced range of motion, decreased repetition number, or substitution of a modified curl-up) to allow for data collection while minimizing discomfort. Any modifications will be recorded in the case report form. Participants who are unable to perform a specific task due to pain or physical limitations will not be forced to complete it. This will be documented as a protocol deviation. Data from modified tasks will be excluded from the primary between-group analyses to ensure comparability of the sEMG measurements. These data will be reported descriptively in Supplementary material.

Offline signal processing will involve band-pass filtering (20–450 Hz) and a 50 Hz notch filter. The root mean square (RMS) value will subsequently be calculated. The %MVIC for each functional task will be determined by normalizing the RMS value to the maximum RMS obtained during MVIC. %MVIC will reflect the level of muscle activation. MPF is a sensitive frequency-domain indicator of local muscle fatigue, with a decrease signifying fatigue. In this study, changes in MPF during functional tasks before and after the intervention will be compared to evaluate muscle anti-fatigue capacity.

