**Methods and analysis:**

This single-center, assessor-blinded RCT will enroll 50 participants randomized 1:1 to control (health education + lumbopelvic manipulation) or experimental group (same plus Baduanjin). The control group will receive lumbopelvic manipulation (15 min/session, three times per week), while the experimental group will receive the same manipulation plus supervised Baduanjin exercise (12 min/session, three times per week) for 4 weeks. The 4-week intervention is followed by follow-up assessments at weeks 8 and 12. Primary outcome: pain intensity (Numerical Pain Rating Scale, NPRS). Secondary outcomes: functional disability (Oswestry Disability Index, ODI), quality of life (SF-36), and sEMG parameters (%MVIC and mean power frequency, MPF) of the lumbar extensors (erector spinae and multifidus) and abdominal wall muscles (rectus abdominis, external/internal oblique, and transversus abdominis). Assessments at baseline (week 0) and week 4; NPRS, ODI, SF-36 also at weeks 8 and 12.

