If the hypotheses are supported, this study may offer a safe, non-pharmacological option for breastfeeding women with PLBP. This population often faces greater caution with medication use during lactation. The sEMG data may also provide biomechanical evidence for the concept of “bone alignment and tendon flexibility” (Gu Zheng Jin Rou in Chinese)—a traditional Chinese medicine principle emphasizing the interdependence between structural alignment and neuromuscular function. This could facilitate the acceptance of traditional Chinese exercise therapy in Western rehabilitation settings.

Several limitations should be acknowledged. First, due to the nature of manual therapy and Baduanjin exercise, blinding of participants and treating therapists is not feasible. However, outcome assessors and the statistician will remain blinded throughout the trial to minimize detection bias. Second, the follow-up period is limited to 8 weeks after treatment, which precludes the evaluation of very long-term effects. Additionally, sEMG assessments are performed only at baseline and week 4, whereas clinical outcomes are followed to week 12. This difference reflects the aim of capturing immediate neuromuscular adaptations during the active intervention phase while minimizing participant burden, but it limits our ability to assess whether these adaptations are sustained during the follow-up period. Third, sEMG signals are collected only from selected core muscles (erector spinae, multifidus, rectus abdominis, external/internal oblique, and transversus abdominis) and do not include the pelvic floor muscles, which also play a crucial role in lumbopelvic stability. Fourth, the sample size (25 per group) may limit subgroup analyses, such as comparing primiparous vs. multiparous women or different delivery modes. Additionally, the inclusion of only primiparous and secundiparous women may limit the generalizability of our findings to women with higher parity. The correlation analyses examining associations between pain, functional outcomes, and sEMG parameters are exploratory in nature and intended to generate hypotheses for future studies. As these analyses were not prespecified in the trial registration, the results should be interpreted with caution.

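### A group difference in the surface-EMG outcome labelled transversus abdominis cannot be attributed to that muscle, because nothing in the protocol separates it from the overlying internal oblique

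*Protocol article*

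**What the plan says.** Section 2.8.4 sets the recording sites: "Surface EMG signals will be recorded from the bilateral erector spinae, multifidus, rectus abdominis, external oblique, internal oblique, and transversus abdominis". Internal oblique and transversus abdominis are separate entries in that list.

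The same section assigns tasks to muscles. Part of that list reads "supine rotational curl-up against resistance (external and internal obliques), and abdominal drawing-in (transversus abdominis". The two obliques share the resisted rotational curl-up, and drawing-in belongs to transversus abdominis only.

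The abstract (Methods and analysis) gives %MVIC and MPF as secondary outcomes for the lumbar extensors and for the "abdominal wall muscles (rectus abdominis, external/internal oblique, and transversus abdominis". The last paragraph of the Introduction gives the same six muscles. Section 2.8 repeats the two sEMG parameters as secondary outcomes without naming muscles.

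On interpretation, section 2.8.4 says of the percentage measure that "MVIC will reflect the level of muscle activation". It reads a fall in MPF as local muscle fatigue.

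The limitations in the Discussion say that "sEMG signals are collected only from selected core muscles (erector spinae, multifidus, rectus abdominis, external/internal oblique, and transversus abdominis", and name the missing pelvic floor muscles and the absence of sEMG after week 4. They do not mention muscle depth or crosstalk. Ultrasound appears only as an idea for future work, to measure muscle thickness.

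**The concern.** The plan attaches a muscle's name to an outcome and says what the number means: the activation of that muscle. For transversus abdominis the name claims more than a skin electrode can deliver. It is the deepest layer of the abdominal wall, with the internal oblique over it, so what is recorded at the skin is a mixture.

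What is at stake is how a result would be worded. If the experimental group showed a higher value in drawing-in, the outcome label would lead to a statement about transversus abdominis activation. The data would fit equally well with a change in the internal oblique, or in both.

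A difference in this channel is also plausible. Section 2.7.2 has therapists cue the Baduanjin participants to draw the abdomen inward, which resembles the test task, and the control group is not described as receiving that cue. Section 2.12 also enters %MVIC and MPF into the exploratory correlations with pain, disability and quality of life, so the label would carry over there.

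**Working it through.** The protocol states no figure on this point, so there is none to reproduce. The check is whether any step in the plan could separate the two muscles.

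**Premise from outside the documents.** Transversus abdominis lies under the internal oblique. The protocol does not say so. It is basic anatomy and depends on none of the cited sources.

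**Steps that might separate the signals (all section 2.8.4):**

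1. *Electrode position.* The rule is "Electrodes will be positioned in accordance with SENIAM guidelines (25". A position rule decides where on the skin the signal is picked up. It does not remove a layer lying between the skin and the target.
2. *Filtering.* A 20–450 Hz band-pass and a 50 Hz notch are specified. They are fixed frequency filters, and nothing in the plan suggests that the two muscles occupy different bands.
3. *Task.* Drawing-in is assigned to transversus abdominis. Nothing in the plan excludes or measures internal oblique activity during it.
4. *Normalisation.* For the reference contraction, "participants will perform resisted movements specific to each muscle (e.g., prone resisted trunk extension and supine resisted curl-up". Write T and O for the transversus and oblique contributions to mean-square amplitude at the electrode and treat them as uncorrelated. Then
   - %MVIC = 100 × √(T_task + O_task) / √(T_max + O_max).
   - A single observed value depends on both contributions, above and below the line. Normalising rescales the mixture and does not unmix it.
5. *MPF.* Under the same assumption, with f_T and f_O the mean frequencies of the two sources,
   - MPF = (T × f_T + O × f_O) / (T + O).
   - If f_T and f_O differ, the value can move because the shares of T and O have changed, with no change in fatigue in either muscle.
6. *Independent check.* No fine-wire recording, concurrent ultrasound or crosstalk procedure is described.

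None of the six resolves the mixture.

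**Extent.**
- Muscles: 1 of 6.
- Bilateral sites: 6 × 2 = 12, of which 2 are labelled transversus abdominis.
- Muscle-by-parameter outcomes, if left and right are analysed separately: 12 × 2 = 24, of which 2 × 2 = 4.
- If the sides are averaged: 6 × 2 = 12, of which 2.

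The protocol does not say how sides are handled. The share is one sixth either way. These counts take each muscle in its assigned task only.

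**The case against.** The strongest reply is about weight. The Discussion treats the abdominal recordings as material for exploratory analysis and puts the main sEMG focus on multifidus and erector spinae. Its account of fatigue resistance is built on the lumbar extensors. No section announces a transversus-specific conclusion. All of this stands and limits how serious the point is. It does not make the label valid, because the abstract still lists the muscle under secondary outcomes and section 2.8.4 still reads %MVIC as muscle activation.

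A second reply is that the cited electrode guideline or the supplementary manual may give a transversus site and reference contraction. Neither can be checked here, and the missing detail is not held against the plan. A better-specified site would still have the internal oblique over the target.

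Third, the documents give no figure for how much the internal oblique contributes during drawing-in. That is correct: the share is unknown. The point does not need it to be large, only that the plan has no means of knowing it.

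A reader might also infer three stronger things that the documents do not support:

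- *That one signal is reported twice, so all internal oblique and transversus outcomes are non-independent.* The internal oblique is read during the rotational curl-up and the transversus site during drawing-in. These are different contractions recorded at separately listed sites. Crosstalk blurs the transversus label but does not make the two outcomes the same data.
- *That the trial's mechanism rests on transversus abdominis.* The Discussion places the emphasis on the paraspinal muscles.
- *That the protocol already plans to count the two muscles as separate confirmations.* It does not say so. It leaves that reading open.

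**Conclusion.** The point holds as a matter of labelling and interpretation. As written, the plan assigns a mixed surface signal to one muscle, and a between-group difference in it cannot be attributed to transversus abdominis specifically. Agreement between this outcome and the internal oblique outcome could not be read as evidence from two distinct muscles either, because internal oblique activity may contribute to both.

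The size is one of six named muscles, within a secondary sEMG outcome whose abdominal part is described as exploratory. The NPRS primary analysis, the sample size in section 2.11 (which rests on NPRS), ODI, SF-36 and the erector spinae and multifidus recordings are untouched.

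The conclusion rests on the anatomical layering and on the absence, in the article, of any step that separates the two signals. It does not rest on what the electrode guideline says or on an assumed size of the internal oblique contribution. The change should be made before results are reported, but it does not threaten the trial's main question.

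**What to change.** - Label the drawing-in outcome *transversus abdominis/internal oblique (combined)* in the abstract, the last paragraph of the Introduction, section 2.8.4 (both the list of muscles and the task now given as "abdominal drawing-in (transversus abdominis") and the limitations in the Discussion. Section 2.8 names no muscles and needs no change.
- State in section 2.8.4 that no transversus-specific conclusion will be drawn from this outcome, and that it will not be counted as confirmation independent of the internal oblique outcome.
- Use the combined label in the section 2.12 correlations.
- Add one sentence to the sEMG limitations: the muscle's depth and crosstalk from the overlying internal oblique prevent attribution to transversus abdominis alone.

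The cost is wording and table labels. No new procedure, visit, equipment or participant burden is needed, and every planned recording stays usable. The downside is that the trial gives up a transversus-specific claim, which the method could not have supported.

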### Statistical analysis

2.12

All statistical analyses will be performed using SPSS version 26.0. Primary analyses will be conducted on an intention-to-treat (ITT) basis, including all randomized participants in their originally assigned groups regardless of protocol adherence or withdrawal. Missing data will be handled via multiple imputation (MI), the gold-standard approach for missing continuous clinical outcome data in randomized controlled trials. Last observation carried forward (LOCF) will not be adopted in the present study, as this single-imputation method is prone to bias and has been widely discouraged in contemporary statistical guidelines. Continuous variables will first be tested for normality using the Shapiro-Wilk test. Normally distributed data will be reported as mean ± standard deviation (SD), whereas non-normally distributed data will be presented as median (first quartile, third quartile) [M (P25, P75)]. For within-group comparisons, paired-sample t-tests will be applied to normally distributed data, and Wilcoxon signed-rank tests to non-normally distributed data. For between-group comparisons at baseline, independent-sample t-tests will be used for normally distributed data, and Mann-Whitney U tests for non-normally distributed data. To compare post-intervention outcomes between the two groups, analysis of covariance (ANCOVA) will be performed, with baseline values as covariates to adjust for potential baseline imbalance. In addition, potential confounding variables—including postpartum duration (months since delivery), age, and baseline outcome values—will be recorded and considered as covariates in the primary analyses where appropriate. Exploratory correlation analyses will employ Pearson or Spearman correlation coefficients, as appropriate, to examine associations among post-intervention pain intensity (NPRS), the Oswestry Disability Index (ODI), the SF-36, core muscle activation (%MVIC), and mean power frequency (MPF). These analyses are hypothesis-generating and will be interpreted with caution; formal corrections for multiple comparisons will not be implemented. All tests will be two-sided, and a *P*-value < 0.05 will indicate statistical significance. Given the exploratory nature of these analyses and the multiple comparisons involved, the results should be interpreted as hypothesis-generating, and any statistically significant findings will require confirmation in future studies.

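### Week-4 sEMG values from pain-modified tasks are dropped from the between-group comparison, so the affected muscle comparisons lose randomised participants on an event driven by the primary outcome

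*Protocol article*

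**What the plan says.** Section 2.8.4 of the protocol article sets the timing of the sEMG tests: "Measurements will be taken before the intervention and after 4 weeks of training". It then gives the trigger for changing a task: "If a participant reports pain that prevents completion of a task as described, the task may be modified". Its examples are a smaller range of motion, fewer repetitions and a substituted curl-up. Some tasks may not be done at all: "Participants who are unable to perform a specific task due to pain or physical limitations will not be forced to complete it"; these are logged as protocol deviations. For values that were obtained from a modified task, the rule is "Data from modified tasks will be excluded from the primary between-group analyses to ensure comparability of the sEMG measurements", followed by "These data will be reported descriptively in Supplementary material".

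Section 2.8 gives the standing of the outcomes: "The primary outcome is pain intensity, measured using the Numerical Pain Rating Scale (NPRS"), while sEMG (%MVIC and MPF) is secondary. Section 2.12 describes the primary analyses as intention-to-treat, "including all randomized participants in their originally assigned groups regardless of protocol adherence or withdrawal", and sends missing data to multiple imputation. Nothing in the article says that excluded modified-task values count as missing for that purpose.

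**The concern.** An exclusion is harmless to a randomised comparison when it cannot depend on treatment. This one can. The week-4 test comes after four weeks of treatment, the trigger is pain, and the trial is designed to detect a difference in pain between the arms. If the experimental arm has less pain, fewer of its tasks will need modification and more control values will be discarded. For each affected task, the controls who remain are then those with less pain, and they are compared with a nearly complete experimental arm.

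At stake is the trial's secondary objective, the exploration of neuromuscular mechanisms by sEMG, which the Discussion presents as the trial's new contribution. With 25 per arm, even a few values lost selectively per task matter.

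**Working it through.** **1. The rules side by side.** Section 2.12 keeps all randomised participants and imputes what is missing. Section 2.8.4 removes recorded values from a between-group analysis and moves them to descriptive reporting. For a muscle whose week-4 task was modified, both cannot be followed unless the removed value is declared missing and imputed. No sentence does that.

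**2. Which visit matters.**
- *Baseline.* Section 2.5 opens the envelope only after all baseline assessments. Its list of examples does not name sEMG, but Table 1 places sEMG at baseline and section 2.8.4 places it before the intervention. Treatment cannot have influenced a baseline modification. Its cost is precision and a missing ANCOVA covariate.
- *Week 4.* Modification here follows randomisation and treatment. The problem lies at this visit.

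**3. Design inputs from the document.** Section 2.11 gives a difference of 2 NPRS points, SD 2.3 (of change scores), two-sided 0.05 and 80% power. These reproduce the stated figure of about 22 per group: 2 × (1.960 + 0.842)² × 2.3² / 2² = 20.8, so 21 by the normal approximation and 22 with the t distribution. The article gives no modification rate, no pain–sEMG correlation and no sEMG effect size.

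**4. Illustration under assumptions.** Assume week-4 pain is normal with SD 2.3 (borrowed from the change scores), with means 4 (control) and 2 (experimental). Assume also that a task is modified when pain reaches a cut c, and that the sEMG value correlates −r with pain within each arm.

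For an arm with mean m, let z = (c − m)/2.3.
- Share excluded = 1 − Φ(z).
- Among those kept, mean standardised pain falls by λ = φ(z)/Φ(z), so mean sEMG rises by r × λ.
- Shift in the between-arm difference = r × (λ_exp − λ_ctrl).

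With c = 6:
- Control: z = 2/2.3 = 0.870; excluded 19.2%; λ = 0.338.
- Experimental: z = 4/2.3 = 1.739; excluded 4.1%; λ = 0.092.
- Shift = r × (0.092 − 0.338) = −0.247r from unrounded values. At r = 0.4 this is −0.10 SD.

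If the whole sEMG effect ran through pain, the true difference would be 0.4 × 2/2.3 = 0.35 SD, and the analysis after exclusion would show 0.25 SD.

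**5. Range.** The same formula, for r from 0.3 to 0.7:

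| Week-4 means (control, experimental) | Cut | Excluded: control | Excluded: experimental | Shift (SD) |
|---|---|---|---|---|
| 4, 2 | 7 | 10% | 1.5% | −0.05 to −0.11 |
| 4, 2 | 6 | 19% | 4% | −0.07 to −0.17 |
| 4, 2 | 5 | 33% | 10% | −0.11 to −0.25 |
| 5, 3 | 7 | 19% | 4% | −0.07 to −0.17 |
| 5, 3 | 6 | 33% | 10% | −0.11 to −0.25 |
| 5, 3 | 5 | 50% | 19% | −0.14 to −0.32 |

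A simulation with 500,000 per arm agrees. A true sEMG effect of 0 comes out at −0.05 to −0.32 SD, and a true effect of 0.5 SD at 0.18 to 0.45 SD. Imputing the dropped values from week-4 pain within arm returns about 0 and 0.5 SD. That recovery holds because the simulated exclusion depends on pain alone.

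**6. Scale.** With 25 per arm, the unadjusted standard error of a difference in SD units is √(2/25) = 0.28. The middle case of 0.10 SD is about a third of that, and the largest shift, 0.32 SD, slightly exceeds it.

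**The case against.** The strongest reply is that a modified task is a different measurement. A smaller range of motion or a substituted curl-up changes the load and hence %MVIC, so keeping such values as if they were standard would be wrong. One may also read sections 2.8.4 and 2.12 together: an unusable value is missing, and missing values are imputed. The comparability reason stands for those two modifications. It is weaker for fewer repetitions, since %MVIC is averaged over repetitions and fewer standard ones still estimate the same quantity. The joint reading is possible, but the text does not state it. The values are recorded, excluded and then described.

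Four stronger readings are tempting, and the documents do not support them:
- *The trial's primary analysis is compromised.* The rule uses the word primary, but it concerns sEMG, a secondary outcome. NPRS is analysed separately.
- *The women in most pain are removed from the trial's comparison.* The exclusion works task by task, so a woman with a modified curl-up may still contribute trunk extension. The illustration therefore describes one task's comparison.
- *Baseline exclusions also bias the contrast.* They precede treatment and do not by themselves do so.
- *The pain–sEMG correlations are truncated.* The rule is limited to between-group analyses, and nothing extends it to the exploratory correlations.

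The size and sign are also open. The real trigger is pain that stops a specific 3-second task, not an NPRS cut. The denominator of %MVIC is a maximal effort that pain may also reduce, so %MVIC could rise with pain and reverse the direction. MPF may behave differently again. Baseline adjustment by ANCOVA is not in the illustration.

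**Conclusion.** The point holds for the week-4 sEMG comparisons. The plan fixes a rule that discards values on a post-randomisation event tied to the primary outcome, and it conflicts with the plan's own all-randomised principle unless those values are imputed, which it does not say. If the arms differ in pain, unequal exclusion is likely. The amount and direction of bias cannot be derived from the documents. With a 2-point pain difference, SD 2.3, a threshold trigger and a negative pain–sEMG correlation of 0.3 to 0.7, the shift is 0.05 to 0.32 SD against the experimental arm; with a positive correlation it would run the other way. This merits a correction because the remedy is cheap and sEMG carries the secondary objective. It gives no reason to doubt the NPRS result.

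**What to change.** In sections 2.8.4 and 2.12, state that week-4 sEMG values from modified or unperformed tasks are treated as missing for that task and imputed under the planned multiple imputation. The model should contain arm, baseline sEMG, and baseline and week-4 NPRS, so that all randomised participants stay in each sEMG comparison. Add one sensitivity analysis that uses the modified-task values as recorded. Report the number of modified and unperformed tasks by arm and visit as a result.

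The cost is a few sentences and one extra analysis run. The case report form already records modifications, and NPRS is already measured at both visits, so no new data are needed. There are two drawbacks. Imputation assumes that the values are missing at random given pain and the other model variables, which cannot be verified. The recorded values used in the sensitivity analysis are less comparable than standard ones, which is why they belong there and not in the main comparison.

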## Discussion

3

This study protocol presents a randomized controlled trial evaluating the efficacy and neuromuscular mechanisms of lumbopelvic manipulation combined with Baduanjin exercise for postpartum low back pain. The ‘prepare-then-train' sequence is grounded in clinical experience and theoretical reasoning, although direct comparative evidence is currently limited (15). This study is designed to provide objective sEMG evidence to test this hypothesis.

Given the limited data on postpartum populations and the scarcity of objective neuromuscular assessments in this field (9), our protocol addresses these gaps by combining validated patient-reported outcomes (NPRS, ODI, SF-36) with quantitative sEMG parameters (%MVIC and MPF). This design allows us to assess whether improvements in pain and function are accompanied by objective changes in core muscle activation and fatigue resistance.

Assessing muscle fatigue and endurance is particularly relevant in the postpartum population (26). Pregnancy and childbirth lead to reduced endurance of the core musculature which compromises spinal and pelvic stability (27). Compounding this physiological decline, postpartum women face substantial physical demands, including frequent bending, lifting, and carrying of the infant, as well as breastfeeding, all of which impose repetitive loads on the lumbopelvic region and may accelerate muscle fatigue (28). Therefore, evaluating changes in MPF—a sensitive frequency-domain indicator of muscle fatigue—provides insight into whether the combined intervention improves the ability of the lumbar extensor muscles to resist fatigue during functional tasks, which may be a key mechanism underlying its therapeutic effects.

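### The averaged mid-hold MPF mixes starting level with any decline, so its change from week 0 to week 4 cannot be attributed to fatigue resistance

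*Protocol article*

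**What the plan says.** All of the measurement detail is in section 2.8.4 of the protocol article.

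- **Task:** "Each movement will be held for 3 s and repeated three times".
- **Rest:** "A 1-min rest interval will be provided between each functional task to minimize muscle fatigue". A further 2 min precedes the first MVIC trial. No rest is stated between the three repetitions of a task.
- **Index:** MPF comes from a "1-s epoch centered on the middle of each 3-s contraction) and averaged across the three repetitions".
- **Timing:** "Measurements will be taken before the intervention and after 4 weeks of training".
- **Meaning given to MPF:** "MPF is a sensitive frequency-domain indicator of local muscle fatigue, with a decrease signifying fatigue".
- **Use made of it:** "changes in MPF during functional tasks before and after the intervention will be compared to evaluate muscle anti-fatigue capacity".

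The last paragraph of the Introduction likewise says that sEMG will quantify fatigue resistance. The Discussion says that MPF gives insight into "whether the combined intervention improves the ability of the lumbar extensor muscles to resist fatigue during functional tasks", and offers this as a possible key mechanism. Section 2.8 lists MPF as one of two sEMG parameters among the secondary outcomes.

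**The concern.** If a fall in MPF is the sign of fatigue, then better resistance to fatigue should appear as a smaller fall while the muscle is working. The article describes no sustained or fatiguing contraction, no MPF slope, and no contrast between the start and end of a hold or between the first and last repetition. It fixes a single averaged level per visit and compares levels four weeks apart.

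What is at stake is the mechanistic conclusion. The trial's secondary objective is to explore neuromuscular mechanisms, and the Discussion presents the sEMG parameters as objective evidence on activation and fatigue resistance. If the plan is followed as written, a rise in MPF in the experimental group would be reported as improved fatigue resistance when the index cannot show which quantity moved. The limitations paragraph of the Discussion does not mention this.

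**Working it through.** The plan gives no figure to reproduce here. The check concerns what the index can identify.

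**Inputs from section 2.8.4.** Hold 3 s; three repetitions; one 1-s epoch centred in each hold (1.0 to 2.0 s); average over repetitions; two visits.

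**Time under load and time analysed, per task.**
- Contraction: 3 × 3 s = 9 s.
- Analysed: 3 × 1 s = 3 s, always at the same position in the hold, reduced to one mean.

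**Model within a hold.** Let MPF(t) = f0 + s·t, where f0 is the starting level and s < 0 is a decline. The mean over 1.0 to 2.0 s is f0 + 1.5·s. If each repetition starts recovered (an assumption), averaging three repetitions returns the same value.

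**Illustration.** The article gives no MPF values, so these are assumed:

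| Starting level f0 (Hz) | Slope s (Hz/s) | Index f0 + 1.5·s (Hz) |
|---|---|---|
| 80 | 0 | 80.0 |
| 80 | −0.2 | 79.7 |
| 80 | −0.5 | 79.25 |
| 80 | −1.0 | 78.5 |
| 78.5 | 0 | 78.5 |

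The last two rows give the same index, although one muscle declines and the other does not.

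**Change between visits.** The change in the index is Δf0 + 1.5·Δs. Take week 0 as f0 = 80 and s = −1.0, giving 78.5 Hz. If the decline halves to −0.5 with f0 unchanged, week 4 gives 79.25 Hz, a rise of 0.75 Hz. If instead the decline stays at −1.0 and f0 moves to 80.75, week 4 gives 80.75 − 1.5 = 79.25 Hz, the same rise of 0.75 Hz. The index cannot tell these apart.

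**If repetitions are not recovered.** Suppose the starting level drops by d from each repetition to the next. The three values are f0 + 1.5·s, f0 + 1.5·s − d and f0 + 1.5·s − 2d, and their mean is f0 + 1.5·s − d. The build-up of fatigue is then in the index, but mixed with level and slope. Repetition 3 minus repetition 1 equals −2d, which does isolate it. Averaging discards that contrast.

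**Between-group analysis.** Adjusting the week 4 value for baseline, as section 2.12 plans, estimates a group difference in the same composite. Randomisation protects that comparison; it does not say which component differs.

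**The case against.** The case on the other side has real substance, and it limits how far the point can go.

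- **Rest.** A reader might infer that the contractions are rested and the muscle unfatigued. The article does not say so. The 1-min interval separates different tasks and limits carry-over between them. Repetitions within a task may run back to back, so some fatigue may build up over the 9 s.
- **Averaging.** A reader might infer that averaging removes any decline, or that a null MPF result would say nothing at all about fatigue. That is too strong. The slope stays in the index as 1.5·s, and a drop between repetitions stays in it as d. What is supported is that level and decline cannot be separated.
- **Definition.** The article equates a fall in MPF with fatigue, but does not itself define fatigue resistance as a within-session slope. Reading it so is an inference, although the natural one from its own definition.
- **Weight.** MPF is secondary and exploratory. The Discussion is hedged and confines this claim to the lumbar extensors. Its remarks on endurance are background rationale, not a conclusion drawn from MPF.

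All four stand as limits. None supplies the missing step: nothing in the article turns the averaged level into a measure of how well a muscle withstands fatigue, and section 2.8.4 states that interpretation without a hedge.

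**Conclusion.** The point holds in this form: the averaged mid-hold MPF does not isolate a fatigue decline, so its change from week 0 to week 4 cannot be attributed to anti-fatigue capacity or to a finding that treatment "improves the ability of the lumbar extensor muscles to resist fatigue during functional tasks". It can still be reported as a change in spectral level during brief contractions.

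The conclusion rests on the index as fixed in section 2.8.4 and on the article's own statement of what a fall in MPF means. The linear model and the Hz values are illustrative assumptions; the non-separability does not depend on the values chosen. Whether 3-s holds produce a measurable decline cannot be settled from the article.

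The consequence is confined to the interpretation of one secondary outcome. The NPRS primary analysis and the sample size are unaffected.

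**What to change.** 1. In the last paragraph of the Introduction, in section 2.8.4 and in the Discussion, describe MPF as a spectral level during brief contractions. Remove fatigue resistance as something concluded from it.
2. Optionally, prespecify one exploratory within-session contrast for the functional tasks: mid-hold MPF in repetition 3 minus repetition 1, compared between groups at week 4 with its baseline value as covariate. State that 3-s holds may show little decline, and that the contrast captures change across repetitions, not within a hold. Record the rest given between repetitions so that it can be interpreted. Tasks performed with fewer repetitions are already set aside as modified under section 2.8.4.

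The cost is a few wording changes and, for the option, keeping the per-repetition MPF values that are computed anyway before averaging. No extra testing of participants is needed. The downside is a narrower mechanistic claim. The change should be made before analysis, since a contrast added afterwards would look data-driven.
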